**7) Labeling of ADSCs with ^99 m^Tc-HMPAO (^99 m^Tc-ceretec)**: To visualize ADSCs within the lung, in a representative number of patients (n = 4), we will label them with ^99 m^Tc-HMPAO (^99 m^Tc-ceretec) according to a modified protocol [32]. A fraction of isolated ADSCs will be diluted into a 5 cc syringe with sodium chloride 0.9% and incubated with a vial containing 0.5 mg of ceretec reconstituted with approximately 2.0 mCi of free technetium (^99 m^TcO_4_^-^) and prepared to be infused within the right lung. A second syringe containing unlabeled ADSCs and 5 mL sodium chloride 0.9% reconstituted with approximately 2.0mCi ^99 m^TcO_4_^- ^and prepared to be administered into the left lung serving as control sample. As depicted in Figure 2 and as was expected, signal intensity was much stronger in the right lung and this effect remained even 24 hours after the infusion, indicating the presence of ADSCs (Figure 1).

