**Figure 2 F2:**
[figure not shown]
**99mTc lung scintigraphy at different time points (30 min, 90 min and 24 hours) after endobronchial infusion of adipose derived mesenchymal stem cells (ADmSCs)**. Retention of radiolabeled cells (99mTc-HMPAO) (right lung-RT) in comparison to cells with free 99mTcO4 (without ceretec-HMPAO) (left lung-LT) was estimated with computerized image analysis by drawing regions of interest (roi) and calculating the average counts/pixels (aver.count). As depicted in panels A (anterior view) and B (posterior view), signal intensity was significantly stronger in the right lung compared to left lung (roi 334.65 vs. 93.69, respectively), 30 minutes after endobronchial infusion of ADmSCs and this difference remained 90 minutes (panels C and D) (roi 227.24 vs. 37.89, respectively), as well as 24 hours (panels E and F) (roi 14.76 vs. 1.22, respectively) after the infusion, indicating the presence of radiolabeled ADmSCs (99mTc-HMPAO). On the contrary, ADmSCs instilled within the left lung were reconstituted only with free technetium (^99 m^TcO_4_^-^) without ceretec-HMPAO and therefore produced minimal signal intensity within the lung. Free technetium uptake by the stomach is a normal finding due to the presence of free pertechnetate.

**8) Endobronchial Infusion: **The patient will then undergo bronchoscopy using a flexible bronchoscope, under local anesthesia (xylocaine). The flexible bronchoscope will be guided into the lower lobes of both lungs and 1 aliquot of 10 cc SVF cells will be infused using a small catheter (2.0 mm of diameter) through the bronchoscopic channel. Procedure will be repeated thrice at monthly intervals (Figure 1).

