**9) Scintigraphic analysis: **Planar imaging of the lungs in anterior and posterior position will be performed 30 min, 90 min and 24 hours after the administration. At 24 hours single photon emission tomography (SPECT) imaging of the lungs will be also done. Imaging will be implemented in a single-head gamma-camera (GE Millennium MPS, Milwaukee USA) equipped with a low energy high resolution (LEHR) parallel-hole collimator. For planar imaging the matrix size will be set at 256 × 256, while for SPECT at 128 × 128 pixels; the photopeak will be centered at 140 keV, with a symmetrical 20% window. The tomographic imaging parameters consisted of a 360°-rotation angle, a circular technique and an acquisition time of 30 sec per frame. Raw imaging data will be reconstructed using the Butterworth-filtered back-projection algorithm, generating tomographic views of the lungs in the 3 planes (transverse, coronal, and sagittal). In order to estimate the retention of the radiolabeled cells in the lung in comparison to free technetium we will draw regions of interest (ROI's) over the right and left lung in the posterior images at 30, 90 min and 24 hours (Figure 2).

**10) Patient's discharge: **The patient will be discharged 24 hours post-bronchoscopy given that he/she is afebrile and hemodynamically stable, with no signs of infection or any type of allergic reaction.

**11) Clinical, functional and radiological assessment: **Arterial blood gases (ABGs) coupled with clinical (Borg and Medical Research Council-MRC dyspnea scales), health-related quality of life (Saint George's Research Questionnaire-SGRQ and cough assessment test-CAT) and functional (6-minute walking test-MWT, FVC and DL_CO_) assessment will be performed every month after the first infusion until the end of the follow-up period (12 months) and HRCT evaluation 6 months after the first infusion in order to estimate any potential clinical, functional and radiological differences compared to baseline modalities (Table 1).

**Table 1 T1:** Scheduled visits following endobronchial infusion of ADScs

No of Visit	Time-point (days)	ADSCs infusion	Physical Examination	Routine Laboratory tests	MRC dyspnea scale	SGRQ + CAT	6MWT	PFTs	ABGs	HRCT
1	0	1^st^	X	X	X	X	X	X	X	X
2	30	2^nd^	X	X	X	X	X	X	X	
3	60	3^rd^	X	X	X	X	X	X	X	
4	90		X	X	X	X	X	X	X	
5	180		X	X	X	X	X	X	X	X
6	270		X	X	X	X	X	X	X	
7	360		X	X	X	X	X	X	X	X + whole body HRCT scan

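### Both lungs receive ADSCs in the scintigraphy sub-study, so the right-left contrast shows retention of 99mTc-HMPAO activity relative to free pertechnetate, not by itself the presence of cells

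*Protocol article*

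**What the plan says.** Study Methodology, item 7, gives the purpose and the number of patients: "To visualize ADSCs within the lung, in a representative number of patients (n = 4), we will label them with" 99mTc-HMPAO. The two syringes are described as follows.

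- Right lung: a fraction of the isolated ADSCs in saline, "incubated with a vial containing 0.5 mg of ceretec reconstituted with approximately 2.0 mCi of free technetium".
- Left lung: "A second syringe containing unlabeled ADSCs and 5 mL sodium chloride 0.9% reconstituted with approximately 2.0mCi" of pertechnetate, without HMPAO, "prepared to be administered into the left lung serving as control sample".

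Item 7 then draws its conclusion: "signal intensity was much stronger in the right lung and this effect remained even 24 hours after the infusion, indicating the presence of ADSCs". The Figure 2 legend reaches a similar conclusion, worded as the presence of radiolabelled cells. It explains the weak left signal by the tracer: "ADmSCs instilled within the left lung were reconstituted only with free technetium", that is, "without ceretec-HMPAO and therefore produced minimal signal intensity within the lung".

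Item 9 makes the same comparison the planned analysis. It introduces the right-lung and left-lung regions of interest at 30 min, 90 min and 24 h with the words "In order to estimate the retention of the radiolabeled cells in the lung in comparison to free technetium".

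**The concern.** A control that is to show whether cells are present has to differ from the test condition in the presence of cells. Here it does not: both lungs are given ADSCs, and what is varied is whether the technetium is complexed with HMPAO. By the legend's own account, a lung containing cells gave almost no signal. The contrast therefore tracks the tracer, and the cells only to the extent that the tracer is known to be attached to them.

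This matters because the section Aim and hypothesis includes delivering an adequate number of cells to the targeted areas, and scintigraphy is the only measure of cell location that the article describes. As worded, item 7 would reach the same conclusion if part or all of the right-lung signal came from HMPAO complex not bound to cells.

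**Working it through.** **1. The two conditions side by side (item 7)**

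| Component | Right lung | Left lung (control) |
|---|---|---|
| ADSCs | yes | yes |
| Saline 0.9% | yes | yes |
| Technetium activity | about 2.0 mCi | about 2.0 mCi |
| HMPAO (ceretec 0.5 mg) | yes | no |
| Side | always right | always left |

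Presence of cells does not vary. Tracer form and side vary together. Cell numbers are not given for either syringe, so equality of cell dose cannot be confirmed.

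**2. Right/left ratios.** Inputs are the average counts per pixel in the Figure 2 legend.

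- 30 min: 334.65 / 93.69 = 3.57
- 90 min: 227.24 / 37.89 = 6.00
- 24 h: 14.76 / 1.22 = 12.10

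Both lungs carry the same isotope and are imaged at the same times, so physical decay multiplies numerator and denominator equally and cancels.

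**3. Why the ratio grows.** Raw signal at 24 h as a fraction of 30 min:

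- Right: 14.76 / 334.65 = 0.0441, or 4.4%
- Left: 1.22 / 93.69 = 0.0130, or 1.3%
- Quotient: 0.0441 / 0.0130 = 3.39, which equals 12.10 / 3.57

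Signal falls in both lungs, and the left falls 3.39 times further. This figure depends neither on the half-life nor on exactly equal starting activities. It measures slower loss of the HMPAO preparation than of free pertechnetate.

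**4. What a within-lung reading would need.** The article states neither a half-life nor a decay correction. Assume a half-life T of 5.9 to 6.1 h and that the published counts are uncorrected. The formula is

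retained fraction at time t = (C_t / C_0.5h) / 0.5^((t − 0.5)/T)

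| | Decay factor (T = 5.9 to 6.1 h) | Right, raw | Right, corrected | Left, raw | Left, corrected |
|---|---|---|---|---|---|
| 90 min | 0.889 to 0.893 | 67.9% | about 76% | 40.4% | about 45% |
| 24 h | 0.0632 to 0.0692 | 4.4% | 64 to 70% | 1.3% | 19 to 21% |

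For example, right lung at 24 h with T = 5.9 h: 0.0441 / 0.0632 = 0.70; with T = 6.1 h: 0.0441 / 0.0692 = 0.64.

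**5. What follows.** The data are compatible with tracer that stayed bound to cells. They are equally compatible with HMPAO complex that is not bound to cells but is lost more slowly than pertechnetate. The planned contrast cannot separate the two.

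**The case against.** The best defence is that the control does a legitimate, limited job. Item 9 names free technetium as the comparator, and the legend confines its conclusion to radiolabelled cells. The same nominal activity without HMPAO tests whether the right-lung signal could be free pertechnetate, and the answer is no. That stands, and the write-up should keep it. What it does not rescue is the further step in item 7 from tracer to cells.

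Second, item 7 refers to a modified labelling protocol that is not shown. Washing, labelling efficiency and cell-bound fraction may be described there, and a condensed article may leave them out. That also stands, and I make no point of their absence. Such data could support cell-bound tracer independently, but they would not turn the left lung into a control for cells.

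Third, the lack of a stated decay correction might be thought to undermine the contrast. It does not, since decay cancels between the lungs. The article claims only that the difference between them persisted.

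Fourth, a pure side effect large enough to give ratios of 3.57 to 12.10 has no evident mechanism. I agree that this is unlikely to be the main explanation; the confounding is one of design and cannot be examined with the side fixed.

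**Conclusion.** The point holds in a limited form. The contrast supports one statement: activity from the 99mTc-HMPAO preparation is retained longer than free pertechnetate (ratios 3.57, 6.00 and 12.10), so the right-lung signal is not free pertechnetate alone. It does not by itself support presence or retention of cells.

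A reader might infer more, and the documents do not support it:

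- That the cells were not retained. Nothing shows this. Under the assumptions above, 64 to 70% of the right-lung signal remains at 24 h, which is compatible with persistence.
- That HMPAO without cells would give the same picture. The documents give no clearance figure for it; it is an alternative that is not excluded.
- That the legend says pertechnetate leaves the lung. It says only that stomach uptake is normal when free pertechnetate is present. Clearance from the left lung is an inference, though one consistent with the counts.

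The ratios rest only on the published counts. The corrected percentages rest on the assumed half-life and on uncorrected counts. The sub-study enters neither the primary nor the exploratory secondary end-points, so the severity is minor.

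**What to change.** (a) In item 7 and in the Figure 2 legend, replace the conclusion about the presence of cells with: *retention of 99mTc-HMPAO activity relative to free pertechnetate, which does not by itself show cell retention.*

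(b) In item 9, add as the retention measure the decay-corrected signal of the labelled lung at 90 min and 24 h, as a percentage of its own 30 min value, and state the half-life used.

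(c) For any patient not yet imaged, alternate the labelled side. This may come too late: Figure 2 already reports results, and the Discussion reports 12 patients enrolled with six-month data.

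Item (a) costs wording and (b) a fixed arithmetic correction on images already planned. The downside is a weaker cell-tracking claim. I do not propose a cell-free HMPAO comparator, because it would change what is instilled in patients.

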**Figure 2 F2:**
[figure not shown]
**99mTc lung scintigraphy at different time points (30 min, 90 min and 24 hours) after endobronchial infusion of adipose derived mesenchymal stem cells (ADmSCs)**. Retention of radiolabeled cells (99mTc-HMPAO) (right lung-RT) in comparison to cells with free 99mTcO4 (without ceretec-HMPAO) (left lung-LT) was estimated with computerized image analysis by drawing regions of interest (roi) and calculating the average counts/pixels (aver.count). As depicted in panels A (anterior view) and B (posterior view), signal intensity was significantly stronger in the right lung compared to left lung (roi 334.65 vs. 93.69, respectively), 30 minutes after endobronchial infusion of ADmSCs and this difference remained 90 minutes (panels C and D) (roi 227.24 vs. 37.89, respectively), as well as 24 hours (panels E and F) (roi 14.76 vs. 1.22, respectively) after the infusion, indicating the presence of radiolabeled ADmSCs (99mTc-HMPAO). On the contrary, ADmSCs instilled within the left lung were reconstituted only with free technetium (^99 m^TcO_4_^-^) without ceretec-HMPAO and therefore produced minimal signal intensity within the lung. Free technetium uptake by the stomach is a normal finding due to the presence of free pertechnetate.

**8) Endobronchial Infusion: **The patient will then undergo bronchoscopy using a flexible bronchoscope, under local anesthesia (xylocaine). The flexible bronchoscope will be guided into the lower lobes of both lungs and 1 aliquot of 10 cc SVF cells will be infused using a small catheter (2.0 mm of diameter) through the bronchoscopic channel. Procedure will be repeated thrice at monthly intervals (Figure 1).

**9) Scintigraphic analysis: **Planar imaging of the lungs in anterior and posterior position will be performed 30 min, 90 min and 24 hours after the administration. At 24 hours single photon emission tomography (SPECT) imaging of the lungs will be also done. Imaging will be implemented in a single-head gamma-camera (GE Millennium MPS, Milwaukee USA) equipped with a low energy high resolution (LEHR) parallel-hole collimator. For planar imaging the matrix size will be set at 256 × 256, while for SPECT at 128 × 128 pixels; the photopeak will be centered at 140 keV, with a symmetrical 20% window. The tomographic imaging parameters consisted of a 360°-rotation angle, a circular technique and an acquisition time of 30 sec per frame. Raw imaging data will be reconstructed using the Butterworth-filtered back-projection algorithm, generating tomographic views of the lungs in the 3 planes (transverse, coronal, and sagittal). In order to estimate the retention of the radiolabeled cells in the lung in comparison to free technetium we will draw regions of interest (ROI's) over the right and left lung in the posterior images at 30, 90 min and 24 hours (Figure 2).

**10) Patient's discharge: **The patient will be discharged 24 hours post-bronchoscopy given that he/she is afebrile and hemodynamically stable, with no signs of infection or any type of allergic reaction.

**11) Clinical, functional and radiological assessment: **Arterial blood gases (ABGs) coupled with clinical (Borg and Medical Research Council-MRC dyspnea scales), health-related quality of life (Saint George's Research Questionnaire-SGRQ and cough assessment test-CAT) and functional (6-minute walking test-MWT, FVC and DL_CO_) assessment will be performed every month after the first infusion until the end of the follow-up period (12 months) and HRCT evaluation 6 months after the first infusion in order to estimate any potential clinical, functional and radiological differences compared to baseline modalities (Table 1).

**Table 1 T1:** Scheduled visits following endobronchial infusion of ADScs

No of Visit	Time-point (days)	ADSCs infusion	Physical Examination	Routine Laboratory tests	MRC dyspnea scale	SGRQ + CAT	6MWT	PFTs	ABGs	HRCT
1	0	1^st^	X	X	X	X	X	X	X	X
2	30	2^nd^	X	X	X	X	X	X	X	
3	60	3^rd^	X	X	X	X	X	X	X	
4	90		X	X	X	X	X	X	X	
5	180		X	X	X	X	X	X	X	X
6	270		X	X	X	X	X	X	X	
7	360		X	X	X	X	X	X	X	X + whole body HRCT scan

**Abbreviations: **6MWT: 6-minute walking test, ABGs: Arterial blood gases, ADSCs: Adipose-derived stem cells, CAT: Cough Assessment Test, HRCT: High Resolution Computed Tomography, PFTs: Pulmonary Function Tests, SGRQ: Saint George's Research Questionnaire.

### Primary end-points (Safety and Toxicity levels)

The procedure is safe and well tolerated by the patients, as reflected by the absence of signs compatible with infection, allergic reaction, disease acute exacerbation, and ectopic tissue formation, at 12 months after the first post-endobronchial infusion of SVF cells (total follow-up duration for each patients = 12 months).

In particular, patients will be subdivided into three categories depending on the level of toxicity, defined as:

**1) Low level**, including minor side effects such as increased cough, low fever (less than 37.5°C, skin allergic reactions)

**2) Medium level**, including non-life threatening allergic reactions, infections that do not require hospitalization, elevation of liver enzymes or creatinine serum levels.

**3) High level**, including death and/or life threatening major adverse events such as disease acute exacerbations defined as follows:

*a) *If the patient experiences a significant worsening of dyspnea and a decline in exercise tolerance associated with a 10% decrement of their FVC, a 10 mmHg change in PaO_2 _or 50% increase in their oxygen requirement, and a significant progression in their radiographic score between the three month clinic visits;

*b) *If the patient needs to be admitted to the hospital because of worsening respiratory failure requiring mechanical ventilation, worsening gas exchange, or presumed pulmonary infection.

*c) *If the patient develops ectopic tissue formation compatible with carcinogenesis as assessed by whole body computed tomography at 12 months after the first post-endobronchial infusion of SVF cells

Exploratory secondary end-points:

1) Assessment of Forced Vital Capacity (FVC%) predicted.

2) Assessment of Diffuse Lung Capacity for carbon monoxide (DL_CO_%) predicted.

3) Assessment of 6MWT.

4) Assessment of dyspnea scales (Borg, MRC) as well as health-related quality of life questionnaires (SGRQ)

5) Assessment of the disease extent and severity as reflected by chest high resolution computed tomography (HRCT) at 6 and 12 months post-bronchoscopy.

*HRCT (scoring grade 0 = no lesion, grade 1 = less than 5% of the lobe, grade 2: 6-25% of the lobe, grade 3: 26-50% of the lobe, grade 4 = 51-75% of the lobe, grade 5 = 76-100% of the lobe). The "ground-glass" alveolitis will be defined as increased opacification of the lung without obscuration of the bronchial and vascular markings, whereas the fibrosis score will include thickening of the alveolar septa and subpleural areas of honeycombing.

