## Background

IPF is a refractory and lethal form of pulmonary fibrosis characterized by fibroblast proliferation, extracellular matrix deposition, and progressive lung scarring, and comprises the histopathologic pattern of usual interstitial pneumonia (UIP). The incidence of IPF is estimated at 6.8 to 16.3 cases per 100, 000 per year in the United States, and the mean survival from the time of diagnosis is 3 to 5 years regardless of treatment, showing a prognosis worst that than seen in patients lung cancer [1-3].

Although the etiology and pathogenesis of IPF remain poorly understood, current research suggests that the mechanisms driving IPF reflect abnormal, deregulated wound healing in response to multiple sites of ongoing alveolar epithelial injury, involving increased activity and possibly exaggerated responses by a spectrum of proinflammatory and profibrogenic factors [4-10]. So far, despite intense research efforts and clinical trials, there is still no effective treatment that can prolong the survival of patients with IPF [11-14]. Conventional therapeutic approach includes combination of corticosteroids, anti-oxidants, immunosuppressants and immunomodulatory anti-fibrotic agents [11-16]. However, the only, so far, therapeutic approach that has been proven effective in terms of prolonging patient's survival is lung transplantation. Nonetheless, not all the patients with IPF are eligible for lung transplantation whereas there is a significant proportion of these patients that finally succumb while waiting in a lung transplantation list. Therefore, there is critical need for more effective and reliable therapeutic modalities.

Mesenchymal stem cells (MSCs), of different cellular origins (umbilical cord, bone marrow, adipose tissue), represent one of the most challenging and promising areas of novel therapeutic strategies that have been recently applied apart from cosmetic reasons, in several chronic, incurable, fatal diseases such as diabetes mellitus type II, Parkinson's disease, congestive heart failure, renal failure, osteoarthritis and myocardial infarction [17-23].

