### Patients and methods

In our phase Ib dose escalating study will participate 12 with IPF, respectively, based on the recently published diagnostic criteria of ATS/ERS (2011), of mild to moderate disease severity as estimated functional parameters including forced vital capacity (FVC) > 50% and diffusing lung capacity for carbon monoxide (DL_CO_) > 35% of the predicted normal values. All patients will sign an informed consent form where they will agree to their participation in the study and the anonymous usage of their biological fluids for research purposes (see inclusion criteria below).

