**6) Randomization of patients depending on the level of treatment: **To define and standardize the optimal dose regimen that will be both safe and effective we will randomize our 12 patients in the phase I trial into two categories depending on the level of treatment, meaning the number of SVF cells infused per bronchoscopy. In particular we will define as low treatment level the infusion of 0.5 × 10^6 ^SVF cells per kgr of body weight per infusion meaning a total of 1.5 × 10^6 ^SVF cells per kgr of body weight (approximately 120 × 10^6 ^cells in total) and as high treatment level the infusion of 1 × 10^6 ^of SVF cells per kgr of body weight per infusion meaning a total of 3 × 10^6 ^SVF cells per kgr of body weight (approximately 240 × 10^6 ^cells in total). The dose regimen will be based on data arising from previous published studies in patients suffering from myocardial infarction where a dose escalation procedure was applied using a single infusion of 0.5, 1.6 and 5 millions bone marrow mesenchymal stem cells (BM-MSCs) per body weight. Results from the former study demonstrated the absence of a dose-dependent effect while no differences in side-effects between the three studied groups were observed [20]. Moreover, an ongoing clinical trial (the TIME study), with a registration number of NCT00684021, is studying the safety and efficacy of one single dose of intravenously infused 150 million cells in total (meaning 0.5 million cells per kgr of body weight) in patients who had experienced a heart attack. Finally, a recent ongoing clinical trial by Matthay et al [31]. is estimating the safety of two single dose regimens of 5 and 10 million BM -MSCs per kgr of body weight in patients with acute lung injury. Patients in the two randomization groups will be age, sex and disease severity (based on spirometry and HRCT criteria) matched. Our study dose-escalating regimen is in accordance with the existing safety data arising from both published and currently ongoing clinical trials (Figure 1).

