### Basic Principles & Ethical Considerations

The study will be performed in accordance with Institutional Review Board and the Ethics and Scientific Committee of the University Hospital of Alexandroupolis, Democritus University of Thrace standards. Original protocol has already been approved by the Local Ethics and Scientific Committee of the University Hospital of Alexandroupolis, Democritus University of Thrace, Greece (reference number EHD33/1SC/16-02-2010)

Study Duration & Termination

The clinical part of the study will start after the approval of the responsible Ethics Committee and the study initiation visit is performed.

The time frame of the study will be as follows:

• Total Clinical Duration: 24 months

• Recruitment Period of Phase Ib (12 subjects): 12 months

• Treatment + follow-up (per subject): 12 months

The entire study may be prematurely terminated/discontinued if there is:

1. Comprehensive deficiency in the recorded data or protocol compliance so that the study cannot be reliably assessed

2. Occurrence of undesired experiences or adverse events necessitating termination (high toxicity level).

3. The Principal Investigator and the Project Manager commonly decide premature termination, after consultation with the Ethics Committee.

In the event of early termination, Investigator will cease use of the investigational drug immediately. A written statement fully documenting the reasons for such a termination will be provided from the Department of Pneumonology, Democritus University of Thrace to the Institutional Review Boards/Independent Ethics and Scientific Commitees and Regulatory Authorities of the University Hospital of Alexandroupolis, Democritus University of Thrace, Greece.

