So far preliminary data recently presented at the 21^ST ^European Respiratory Society Congress, Amsterdam 2011 in the form of an abstract seem promising and intriguing since none of the 12 patients enrolled in the study experienced any clinically significant cases of infections, allergic reactions, acute exacerbations or other major side effects requiring hospitalization. In addition 6 months follow-up data revealed a marginal improvement at 6MWD and FVC levels [21,37].

The main purpose of this project and consequently this trial is to provide worldwide scientific committee with pivotal safety data regarding this novel therapeutic option and accelerate its application to a larger cohort of patients in the context of multicenter phase II and III clinical trials. There is plenty of room for further technical improvements, development and widespread acceptance and accessibility. However, pilot safety studies are of major importance and represent the first hamper that should be overcome to establish a rigid basis for larger clinical trials where safety concerns will be addressed cautiously and thoroughly and efficacy outcomes of high scientific rigidity will be safely extracted.

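### The primary safety criterion, absence of events, conflicts with the protocol's own toxicity grades, could fail a harmless treatment, and if met still leaves a risk of about one in four open

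*Protocol article*

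**What the plan says.** The section Primary end-points (Safety and Toxicity levels) words the end-point as a conclusion: the procedure is "safe and well tolerated by the patients, as reflected by the absence of signs compatible with infection", allergic reaction, acute exacerbation and ectopic tissue, judged 12 months after the first infusion ("total follow-up duration for each patients = 12 months").

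It then sorts patients into three toxicity levels. Skin allergic reactions are Low. Infections that do not lead to admission are Medium. High is described as "including death and/or life threatening major adverse events such as disease acute exacerbations", and the definitions under it include admission for worsening respiratory failure, worsening gas exchange or presumed lung infection.

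Other relevant statements:
- Patients and methods: "In our phase Ib dose escalating study will participate 12 with IPF", of mild to moderate severity.
- Study Methodology, item 6: "we will randomize our 12 patients in the phase I trial into two categories" by dose. All patients receive cells, and group sizes are not given.
- Background: "the mean survival from the time of diagnosis is 3 to 5 years regardless of treatment".
- Statistical analysis: safety is compared with each patient's own baseline.
- Study Duration & Termination, item 2: the study may be stopped early for "Occurrence of undesired experiences or adverse events necessitating termination (high toxicity level".

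**The concern.** The criterion has three weaknesses as written.

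First, it does not agree with the grading that follows it. A single skin reaction is Low toxicity, yet it already means that allergic reaction was not absent. The reader cannot tell whether such a trial has met its primary end-point.

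Second, some of the listed events arise from the disease itself. Without an untreated group or a stated background rate, an exacerbation caused by IPF counts against the cells in the same way as one caused by the infusion. Baseline cannot supply that rate, because active infection is an exclusion criterion.

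Third, if no event is seen, the wording turns a zero count in 12 patients into a statement that the procedure is safe. That could be over-read when larger trials are planned.

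**Working it through.** The protocol gives no event rate, margin or precision for its 12 patients, so there is no figure to reproduce. The check has three parts.

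**1. Criterion against grades**

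| Event | Absence criterion | Toxicity level |
|---|---|---|
| Skin allergic reaction | broken | Low |
| Infection without admission | broken | Medium |
| Acute exacerbation | broken | High |
| Death | not listed | High |

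The first two rows show the conflict. The last row shows that the two lists do not cover the same events.

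**2. Background deaths, for scale**

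Inputs: n = 12 (Patients and methods); mean survival T = 3 to 5 years (Background); follow-up of 1 year (Primary end-points). Assumptions: constant hazard, independent patients.

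One-year risk p = 1 − exp(−1/T); expected deaths 12p; chance of at least one death 1 − (1 − p)^12 = 1 − exp(−12/T).

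- T = 3: p = 1 − exp(−1/3) = 28.3%; 12p = 3.4; 1 − exp(−4) = 98.2%.
- T = 5: p = 1 − exp(−1/5) = 18.1%; 12p = 2.2; 1 − exp(−2.4) = 90.9%.

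The constant hazard is not in the protocol, so it was varied. For a median, p = 1 − 0.5^(1/T). For a Weibull hazard with shape k and the same mean, scale λ = T/Γ(1 + 1/k) and p = 1 − exp(−(1/λ)^k).

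| Model | p, T = 3 | p, T = 5 | At least one of 12, T = 3 | At least one of 12, T = 5 |
|---|---|---|---|---|
| Constant hazard, T a mean | 28.3% | 18.1% | 98.2% | 90.9% |
| Constant hazard, T a median | 20.6% | 12.9% | 93.8% | 81.1% |
| Weibull, shape 1.5 | 15.2% | 7.4% | 86.2% | 60.2% |
| Weibull, shape 2 | 8.4% | 3.1% | 64.9% | 31.4% |

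The Weibull rows describe the first year after diagnosis. Patients who enter later would lie further along a rising hazard and have a higher risk than these rows show.

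The documents give no rates for the four listed items. If the 12-month risk of any listed event were 5%, 10% or 20% (illustrative), the chance of none in 12 would be 0.95^12 = 54%, 0.90^12 = 28% or 0.80^12 = 7%.

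**3. What a zero count excludes**

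The exact upper limit for 0 of n is 1 − 0.025^(1/n) (two-sided 95%) or 1 − 0.05^(1/n) (one-sided 95%).

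- n = 12: 26.5% two-sided, 22.1% one-sided.
- n = 6 per dose group (an equal split, assumed): 45.9% two-sided, 39.3% one-sided.

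**The case against.** The opposing case has real force on several points.

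- **Events are not shown to be almost certain.** A reader might infer from the survival figure that some event must occur. The 91% to 98% needs a constant hazard; a rising hazard gives 31% to 86%. The figure is for IPF in general from diagnosis, whereas this trial enrols mild to moderate disease with further exclusions. It also measures death, which is not among the four items. This objection stands: the figure shows scale only.
- **The criterion is not blind to harm.** A reader might conclude that it could not identify a harmful treatment. At a 20% risk, 93% of such trials would show at least one event. It is insensitive to smaller risks, not to all of them.
- **A limit of 22% to 26% applies to any study with 0 of 12, and intervals can be left to an analysis plan.** Both are true. The defect is the stated criterion, which treats absence as showing safety; an analysis plan that adds intervals would not change that wording.
- **The grading may be the working end-point and the absence sentence only the hypothesis.** That reading is possible, but the text does not choose it, so the two need reconciling.
- **Termination is discretionary.** A reader might infer that one background death stops the trial. The section says only that the study may be stopped, so this does not follow.
- **The aim "to provide worldwide scientific committee with pivotal safety data regarding this novel therapeutic option" might be read as a claim of proof.** The Discussion also calls the data preliminary and such studies pilots. The adjective is an editorial matter and the point does not rest on it.

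The Discussion also reports no clinically significant events in the 12 patients enrolled. That does not settle the matter. The qualifier is absent from the end-point, and the length of safety follow-up is not stated. Even under the constant hazard, no death by 6 months, the time of the efficacy data, has probability exp(−6/3) = 13.5% to exp(−6/5) = 30.1%.

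**Conclusion.** The point holds in a limited form. The absence criterion and the three toxicity levels disagree about minor events and must be reconciled. Because exacerbation and respiratory admission occur in the natural course of IPF and there is no untreated comparator, a harmless treatment could fail the criterion. How often cannot be stated, since the documents give no background rates for the four items.

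For scale only, and assuming a constant hazard, the protocol's survival figure implies about 2 to 3 deaths in 12 patient-years, with at least one likely (91% to 98%). The chance is lower if the hazard rises with time or because disease is mild to moderate.

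In the other direction, the result needs no survival assumption: 0 of 12 excludes only a risk above 26.5% two-sided or 22.1% one-sided. The 45.9% per dose group rests on an assumed 6 + 6 split.

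**What to change.** Replace absence as the primary criterion with the 12-month incidence of each component and of the worst toxicity level, overall and by dose, each with an exact (Clopper-Pearson) 95% confidence interval. Show all-cause and treatment-related events separately. The protocol already refers to relatedness when it describes follow-up of adverse events (Recording Subject Withdrawals), so the concept is not new to it. Interpret the results against a background rate for IPF of this severity, stated with its source before the data are analysed. Say in the protocol that 0 of 12 cannot exclude a risk of about one in four.

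The discretionary termination item tied to high toxicity should be reconciled with the events expected from the disease itself. No stopping rule is proposed here.

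The cost is a rewording of the end-point, slightly more analysis work and a more modest safety conclusion. No additional patients are needed.
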